## **2.12 Adverse event reporting**

### **2.12.1 Definitions**

AE: Any untoward medical occurrence in a patient enrolled into this study regardless of its causal relationship to study treatment.

### SAE

An SAE is defined as any AE that: results in death; or is immediately life threatening; or requires inpatient hospitalization; or requires prolongation of existing hospitalization; or results in persistent or significant disability/incapacity; or is a congenital anomaly/birth defect.

Important medical events will be considered an SAE when, based upon appropriate medical judgement, they may jeopardize the patient and may require medical or surgical intervention to prevent one of the outcomes listed in this definition.

### Non-SAE

A non-SAE is defined as any AE that: does not result in death; or is not immediately life threatening; or does not require inpatient hospitalization; or require prolongation of existing hospitalization; or does not result in persistent or significant disability/incapacity; or is not a congenital anomaly/birth defect.

SUSAR: A SUSAR is any SAE that is both suspected to be related to the study treatment and is unexpected (i.e. not consistent with applicable product information).

## **2.12.2 Assessment and Documentation of Adverse Events**

For the purposes of this study the investigator is responsible for recording all AEs, regardless of their relationship to study drug, with the following exceptions:

- Conditions that are present at screening and do not deteriorate will not be considered adverse events.
- Abnormal laboratory values will not be considered adverse events unless deemed clinically significant using local laboratory reference ranges(59) and documented as such.

The description of each AE on the CRF will include: A description of the AE; The onset date, duration, date of resolution; Severity (mild, moderate or severe); Seriousness (i.e. is it an SAE?); Any action taken, (e.g. treatment, follow-up tests); The outcome (recovery, death, continuing, worsening); The likelihood of the relationship of the AE to the study treatment (Unrelated, Possible, Probable, Definite).

The severity and relationship of an AE will be assessed as appendix attached. The seriousness of an AE will be assessed by an investigator according to the definition of an SAE with the following exception:

- Hospitalization due to progression of disease will be considered an SAE.

Changes in the severity of an AE will be reported. AEs characterized as intermittent will be documented for each episode. All AEs will be followed to adequate resolution, where possible.

### **2.12.3 Eliciting Adverse Event Information**

Adverse events will be recorded from the time the patient signs the informed consent form until 30 days after the last dose of study medication. At every study visit patients will be asked “How have you felt since your last visit?” in order to elicit any medically related changes in their well-being. They will also be asked if they have been hospitalized, had any accidents, used any new medication or changed concomitant medication regimens. In addition, AEs will be documented from physical examination findings, clinically significant laboratory results or other documents (including correspondence from primary care physicians) that are relevant to patient safety.

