## **2.7 Primary and Secondary Outcome Measures**

The primary outcome of interest will be virological response. The main virological outcome that will be observed will be the proportion of patients in different arms reaching viral loads of < 50 copies/ millilitre at months 2, 3 and 6 (indicating viral suppression) and > 1000 copies/ millilitre at month 6 (indicating virologic failure).

The secondary outcomes will be immunologic response measured by CD4 count and clinical responses measured by morbidity and death from any cause. With the use of ART alone there is an increment of 30% at 3 months in CD4 count from baseline value(56). With the addition of ASA to the ART, it is expected that the CD4 count will rise by > 30% from baseline value at months 3. Other secondary outcome measures will be plasma levels of sCD14 and sP- selectin, percentage

of activated T cells (CD38 positive and HLA-DR positive T cells), percentage of exhausted T-cells (PD-1 positive T cells), percentage adherence to ART and compliance to study medications, adverse events. The levels of sCD14 and sP- selection are expected to drop to those of non- HIV infected population by 6 months(16).

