#### **2.9.6 Subject Withdrawal**

##### **2.9.6.1 Reasons for withdrawal**

The investigator may withdraw a patient from the study treatment procedures if the patient;

- Will be in violation of the protocol and/or
- Will experience an SAE that is related to the study drug and/or
- Will develop, during the course of the study, symptoms or conditions listed in the exclusion criteria and/or

- Will require a medication that is prohibited by the protocol

The investigator will also withdraw all participants from the study treatment if the study is terminated. Patients will be free to withdraw from the study at any time upon their request.

All the patients who will be withdrawn from the study will be followed up to completion of six months of follow up.

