#### **2.9.6.2 Handling of withdrawals and losses to follow- up**

When a patient withdraws from the study, the reasons for withdrawal shall be recorded by the investigator on the relevant page of the CRF. Whenever possible, all patients who will withdraw from the study prematurely will continue to undergo scheduled visits for study assessments (follow-up).

Patients who will fail to return for study assessments will be contacted by the research team in an attempt to have them comply with the protocol. No contact after two documented phone calls to the patient and one to the next of kin will be considered a loss to follow up.

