In the subsequent monthly visits, patients will have medical history taken and clinical examination except height measurement (done only at baseline) done by the study doctor. In each of the monthly visits data on adherence to ARV drugs and compliance to study drugs, AEs, morbidity, mortality and co-medications will be collected. Additionally, patients will get their study medications refill and be counselled on adherence to ART and compliance to study drugs. In visit 0 and in all follow up visits, patients will also be asked to return to the clinics with their study drug boxes and ARV drug bottles in the next follow up visit for pill count. In addition to the aforementioned information, at months 2 and 3 blood samples for HIV viral load will be taken and also results for routine viral load test measurements for month 6 will be traced from the patients' files and/or medical records and will be included in the analysis. For CD4 count blood samples will be taken at 3 months and results for routine CD4 count measurements at month 6 will be traced from the patients' files and/or medical records and will be included in the analysis. For plasma levels of sCD14 and sP- selectin and for biomarkers of T cell activation and exhaustion blood samples will be taken at months 3 and 6. Blood samples for lipid profile, FBP, RFT and LFT will be taken only at 6 months. Urine samples will be taken from female participants for urine pregnancy test (UPT) during each monthly visit to check if they are pregnant.

|            | STUDY PERIOD                      | Screening
and
Randomizati
on | Study
Treatment | Follow- up    |         |         |         |
|------------|-----------------------------------|---------------------------------------|--------------------|---------------|---------|---------|---------|
|            | VISIT NUMBER                      | Visit 0                               | Visit 0            | Visits 1 – 7  |         |         |         |
|            | MONTH                             | Month 0                               | Month 0            | Months
1-6 | Month 2 | Month 3 | Month 6 |
| PROCEDURES | Informed consent                  | X                                     |                    |               |         |         |         |
|            | Demographic
information        | X                                     |                    |               |         |         |         |

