#### **2.11.7 Other assessments**

During clinical evaluation at each monthly visit, the attending clinician will look for occurrence of any AE since the last visit and all the AEs will be recorded in a specially designed form.

Assessment of compliance to study drugs will be by pill count. Patients' remaining monthly tablets of their study drugs will be counted to ascertain compliance at each monthly follow up visit. Overall compliance will be the average of the monthly compliances.

Adherence to ART will be measured based on pill counts. Patients' will be asked to return with the ARV drug bottles every time they come to the clinic for their follow up visits. At each visit, pills remaining in bottles will be counted by the study doctor and the percentage of these pills to the dispensed pills during the previous visit will be calculated based on the dose and the number of days dispensed. The pill count adherence percent will be obtained by dividing the number of pills consumed by the total number of pills dispensed at the last visit and multiplied by 100. Overall adherence will be the average of the monthly adherences. For patients who will not last in the study for all the 6 months, their adherence to ART will be calculated by taking the average of the monthly adherences of months they have been in the study. Greater than 90% overall adherence by pill count will be considered adherence(58).

Morbidity will be defined as health care facility visits for medical attention/ care because of illness and/or the number of admissions to a health care facility/ hospital. At each monthly visit, patients will be asked if they visited any health care facility to seek medical care/ treatment and/ or if they were admitted on medical basis since last visit. The reason for visit or admission will be traced from the patient or medical and/or clinical records respectively.

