### **2.12.4 Serious Adverse Event Reporting**

#### **2.12.4.1 SAEs**

Any SAE occurring in a study participant will be reported to the MUHAS and the National ethical committees within 24-72 hours of occurrence. The safety reporting forms will be completed, signed and submitted by an investigator.

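### The protocol contradicts itself on how long adverse events are recorded for patients who stop study drug early

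*Protocol*

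**What the plan says.** Section 2.12.3 is the only place that gives both a start and an end for AE recording: "Adverse events will be recorded from the time the patient signs the informed consent form until 30 days after the last dose of study medication". The end is tied to each patient's own last dose. The same section also has patients asked about their health at every study visit.

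Section 2.9.6 keeps early stoppers under observation. On patients whom the investigator withdraws, 2.9.6.1 says: "All the patients who will be withdrawn from the study will be followed up to completion of six months of follow up". Section 2.9.6.2 is softer: "Whenever possible, all patients who will withdraw from the study prematurely will continue to undergo scheduled visits for study assessments".

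The visit descriptions put no last-dose limit on AE collection. Section 2.10 reads "In each of the monthly visits data on adherence to ARV drugs and compliance to study drugs, AEs, morbidity, mortality", in a list of what is collected each month. Section 2.11.7 reads "the attending clinician will look for occurrence of any AE since the last visit and all the AEs will be recorded". Table 2.1 ticks the AE check for months 1 to 6, and the form for subsequent visits (Appendix 3, part G) carries an AE table without a cut-off.

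AEs are a listed secondary outcome: section 2.7 ends its list with "compliance to study medications, adverse events". The only analysis population is intention to treat (2.13.2). Stopping can be triggered by events: a related serious AE or the need for a prohibited drug (2.9.6.1), or bleeding (2.15.1).

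**The concern.** A patient who stops study drug at, say, month 2 has two AE end dates: about month 3 under 2.12.3, and month 6 under 2.10, 2.11.7, Table 2.1 and the form. Under the first rule, AE recording ends part-way through follow-up while morbidity and mortality are still collected at the same visits.

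This should be settled in the protocol, because events that were never recorded cannot be recovered by any later analysis plan. It also matters for the comparison of arms. Section 1.1 names gastrointestinal bleeding as a risk of aspirin, and bleeding leads to a stop, so early stopping could plausibly differ between arms. If it did and 2.12.3 were followed, a secondary outcome analysed by intention to treat would be observed for unequal lengths of time.

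The point concerns patients who stop before month 6. It does not concern the 30 days after the month-6 visit for those who complete.

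**Working it through.** The protocol gives no figure for AE observation time, so there is none to reproduce. The sample size of 227 per arm is not involved.

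**Inputs from the protocol.** Treatment and follow-up last six months (2.5), or 183 days by the tablet count (3.2). AE recording ends 30 days, taken as one month, after the last dose (2.12.3). Early stoppers are followed to month 6 (2.9.6.1).

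**Assumed.** The share of patients who stop early in each arm, and when they stop. The protocol gives neither.

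**Step 1: loss for one patient.** For a stop at month *t*, months without AE recording = max(0, 6 − (*t* + 1)).
- Stop at month 1: 6 − 2 = 4 months, 4/6 = 67%.
- Stop at month 2: 6 − 3 = 3 months, 3/6 = 50%.
- Stop at month 5 or later: nothing is lost.

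In days, with a window of min(*t* + 30, 183), stops on day 30, 60, 90, 120 and 153 lose 123, 93, 63, 33 and 0 days.

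**Step 2: average loss if stops are uniform over 0 to 6 months.** The mean is (5 × 5 / 2) / 6 = 12.5 / 6 = 2.083 months, and 2.083 / 6 = 34.7%. In days, 153² / (2 × 183) = 64 days, or 35.0%.

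**Step 3: coverage by arm.** Coverage = 1 − (share stopping) × (mean fraction lost). The higher-stopping arm is given first.

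| Assumed stopping | Uniform stops | Ratio | All stop at month 1 | Ratio |
|---|---|---|---|---|
| 5% v 5% | 98.3% v 98.3% | 1.000 | 96.7% v 96.7% | 1.000 |
| 10% v 5% | 96.5% v 98.3% | 0.982 | 93.3% v 96.7% | 0.966 |
| 15% v 5% | 94.8% v 98.3% | 0.965 | 90.0% v 96.7% | 0.931 |
| 20% v 5% | 93.1% v 98.3% | 0.947 | 86.7% v 96.7% | 0.897 |
| 30% v 10% | 89.6% v 96.5% | 0.928 | 80.0% v 93.3% | 0.857 |

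For 15% v 5% with uniform stops: 1 − 0.15 × 0.347 = 0.948, 1 − 0.05 × 0.347 = 0.983, and the ratio is 0.965. Working in days changes these ratios by about 0.001.

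Timing matters as well as frequency. With 15% stopping in both arms, all at month 1 in one and uniformly in the other, the ratio is 0.900 / 0.948 = 0.949.

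**Step 4: from coverage to the AE comparison.** These are ratios of observed time. They equal the shortfall in recorded events only if the AE rate is the same on and off drug and events are counted without dividing by observed time.

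**Step 5: the alternative rule.** If AEs are recorded to month 6 for everyone, the window is six months in both arms whatever the stopping pattern, for patients who attend.

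**The case against.** A reader might infer that AE recording does stop 30 days after the last dose, and that the AE comparison is therefore biased in favour of aspirin. The documents do not support either step.

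- **Truncation is not certain.** Sections 2.10 and 2.11.7, Table 2.1 and the follow-up form all continue AE collection at monthly visits. Both sites use the same form, so it is speculation that they would collect different data.
- **Unequal stopping is not documented.** The trial is double-blind, patients with asthma, ulcer disease or a predisposition to bleeding are excluded, and section 1.1 says that aspirin's bleeding harms are more likely at high doses than at low ones.
- **A constant event rate may be wrong.** If aspirin causes AEs, the rate should fall after stopping, so the unrecorded months would hold fewer events than the calculation assumes. If rates are taken per observed person-time, a constant rate gives no shortfall at all.
- **The planned tests compare proportions and means (2.13.3), not rates.** A patient who stops because of an AE already counts in the proportion with any AE, so later truncation changes nothing for that patient on that measure. Repeat events and particular event types could still be missed.
- **The gravest events have other routes.** Section 2.12.4.1 sets no end date: "Any SAE occurring in a study participant will be reported to the MUHAS and the National ethical committees within 24-72 hours of occurrence". Admissions and deaths are collected monthly.

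Most of this stands, and it limits the point to a contradiction with a conditional consequence. It does not remove the contradiction. Section 2.12.1 defines a serious AE as a kind of AE, so whether the 30-day limit also covers serious events is unclear. The morbidity and mortality checks do not include the severity and causality assessment required for an AE. Non-serious events that prompt no facility visit would be lost.

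**Conclusion.** The contradiction is real: for early stoppers the AE window ends either 30 days after the last dose or at month 6, depending on the section read. Under a literal reading of 2.12.3, a stop at month 1 loses about 4 of 6 months, and stoppers lose about 35% of follow-up on average if stops are uniform over time. The arm that stops more or earlier would have less AE coverage.

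The imbalance rests on assumed stopping rates. The coverage ratio is about 0.965 at 15% v 5% with uniform stops, 0.931 if all of them stop at month 1, and 1.000 with equal stopping and the same timing. The effect on the AE comparison depends on off-drug event rates and on the measure used, and would be smaller for the proportion with any AE. A bias in favour of aspirin is possible but not shown. The primary outcome, sample size and power are unaffected.

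The correction is still worth making, because it is cheap and lost data cannot be recovered.

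**What to change.** Replace the recording sentence in 2.12.3 with: *AEs are recorded for every randomised participant from consent until the later of the month-6 visit or 30 days after the last dose, whether or not study drug was stopped.* This agrees with 2.10, 2.11.7, Table 2.1 and the follow-up form.

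At the same time, reconcile the follow-up statements. Section 2.9.6.1 gives six months for withdrawn patients, while 2.15.2 gives 12 months for those with a related serious AE. The end of AE recording for that group should be stated once this is settled.

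The cost is one amended sentence and slightly more AE recording at visits that are already scheduled. No visits are added. Patients who no longer attend will still have gaps, since 2.9.6.2 promises continued visits only where possible.

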### **2.12.4 Serious Adverse Event Reporting**

#### **2.12.4.1 SAEs**

Any SAE occurring in a study participant will be reported to the MUHAS and the National ethical committees within 24-72 hours of occurrence. The safety reporting forms will be completed, signed and submitted by an investigator.

#### **2.12.4.2 SUSARs**

All SUSARs occurring in a study participant will be reported in an expedited fashion (i.e. within 15 calendar days of first knowledge), or for fatal or life-threatening events, an initial or full report within 7 calendar days and a follow-up report if necessary, within the 15-calendar day timeframe. An investigator will complete, sign and submit the SUSAR report.”

## **2.13 Statistical Methods**

### **2.13.1 Sample Size estimation**

The required sample size is 227 participants in each treatment arm making a total of 454 participants.

Assuming that the proportion of patients with < 50 copies/ml at 8 weeks in the control group (ARV alone) is 75%(60), then 227 patients will be required, in each study treatment group, if a relative risk for the ARV + ASA treatment group is 1.15, assuming loss to follow up of 10%, a power of 80% and a significance level of 0.05.

| Item                                                                                                | Value                                     |
|------------------------------------------------------------------------------------------------------------|--------------------------------------------------|
| Proportion of patients with < 50 copies/mL at week 8 after ART initiation in the control group (ARV alone) | 75%                                              |
| Relative risk =1.15 for intervention group(ARV + ASA)                                                      | 1.15 (i.e. 86% in intervention group(ARV + ASA)) |
| Expected loss to follow up                                                                                 | 10%                                              |
| Significance level for a two-sided test                                                                    | 0.05                                             |
| Power                                                                                                      | 80%                                              |
| Total patients in each group                                                                               | 227                                              |

### **2.13.2 Population to be analyzed**

The subject population whose data will be subjected to the study to analyses is the intention to treat population.

### **2.13.3 Statistical Analysis Plan**

The data will be double entered into a computer by two different data entry clerks and the entered data will then be verified and cleaned before being subjected to analysis using the SPSS statistical program. Intention to treat analysis will be done.

Chi- square or Fisher's exact test will be used for comparison of proportions and Student's t test for comparison of means between the two treatment groups.

Descriptive statistics will also be used where appropriate. A two tailed P-value of  $<0.05$  will be considered significant.

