**Definitions.**

1. **Adherence to ART** will be defined as greater than 90% adherence by pill count.
2. **Adverse Event (AE)** will be defined as any untoward medical occurrence in a patient enrolled into this study regardless of its causal relationship to study treatment.
3. **Serious Adverse Event (SAE)** will be defined as any AE that results in death; or is immediately life threatening; or requires inpatient hospitalization; or requires prolongation of existing hospitalization; or results in persistent or significant disability/incapacity; or is a congenital anomaly/birth defect.
4. **Non-Serious Adverse Event** will be defined as any AE that does not result in death; or is not immediately life threatening; or does not require inpatient hospitalization; or does not require prolongation of existing hospitalization; or does not result in persistent or significant disability/incapacity; or is not a congenital anomaly/birth defect.
5. **Suspected Unexpected Serious Adverse Reaction (SUSAR)** will be defined as any SAE that is both suspected to be related to the study treatment and is unexpected (i.e. not consistent with applicable product information).
6. **Morbidity** will be defined as number of health facility/ hospital visits for medical attention/ care because of illness and/or number of health facility/ hospital admissions.
7. **All- cause mortality** will be defined as confirmed death of any cause with certification of death by medical practitioner or a verbal or telephone confirmation of death from a relative or friend.
8. **Clinical conditions associated with death** will be defined as those clinical conditions diagnosed within one month prior to or at time of death or were thought to be related to death after review of the medical records.
9. **Low- dose- aspirin (ASA)** will be defined as ASA dosages between 75mg and 325mg taken every day.
10. **Compliance to ASA** will be defined as adherence to ASA therapy for at least 22 days in a month.

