### **1.6.3 Secondary objectives**

The secondary objectives of the proposed study are:

1. To compare the CD4 counts measured at 3 and 6 months among HIV- infected individuals after initiating ARV therapy alone or ARV therapy and 75mg ASA.
2. To compare the plasma levels of immune activation biomarker (sCD14) measured at 3 and 6 months among HIV- infected individuals after initiating ARV therapy alone or ARV therapy and 75mg ASA.
3. To compare the plasma levels of platelet activation biomarker (P- selectin) measured at 3 and 6 months among HIV- infected individuals after initiating ARV therapy alone or ARV therapy and 75mg ASA.
4. To compare percentage of activated T cells (CD38 positive and HLA-DR positive T cells) measured at 3 and 6 months among HIV- infected individuals after initiating ARV therapy alone or ARV therapy and 75mg ASA.
5. To compare percentages of exhausted T cells (PD1 positive T cells) measured at 3 and 6 months among HIV- infected individuals after initiating ARV therapy alone or ARV therapy and 75mg ASA.
6. To compare morbidity among HIV- infected individuals initiating ARV therapy alone or ARV therapy and 75mg ASA.
7. To compare all-cause-mortality among HIV- infected individuals initiating ARV therapy alone or ARV therapy and 75mg ASA.
8. To determine level of adherence to ARV therapy among HIV- infected individuals initiating ARV therapy and ASA or placebo.

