### **2.10 Study Visits and Procedures schedule**

There will be a total of 7 visits for each patient. At visit 0, patients attending CTCs at each site will be informed about the proposed study and will be invited to participate by the study nurses and doctors. Informed consent will be obtained from the patients by the study nurse who is an employee at the respective CTC. After the patient has given an informed consent, he/she will then be asked

to provide their demographic information. For all the male patients, confirmation of eligibility will be after the demographics while for female patients after the medical history they will be asked to provide urine for pregnancy test. A positive test will exclude them from the study. Once one is found eligible, they will be consecutively enrolled into the study followed by medical history and a clinical examination including blood pressure, height and weight measurements. Once the clinical examination is complete, participants will be randomized to the treatment groups and then blood samples will be taken for baseline investigations before initiation of the ARV drugs and the study drugs. The baseline investigations will include RFT, LFT, CD4 counts and FBP which are routinely taken before initiation of ART. In addition, specifically for this study, blood samples for viral load, lipid profile, plasma levels of sCD14 and sP- selectin, biomarkers of T cell activation and exhaustion will be taken at baseline.

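### CD4 and the activation markers are to be compared by an unadjusted t test although each has a baseline value; baseline-adjusted analysis would be more precise and would correct chance imbalance

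*Protocol*

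**What the plan says.** Protocol section 2.13.3 (Statistical Analysis Plan) gives chi-square or Fisher's exact test for proportions and Student's "t test for comparison of means between the two treatment groups", with a two-sided 5% level. The Abstract names the same tests. Neither place mentions a covariate or a model.

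Secondary objectives 1 to 5 in section 1.6.3 are tied to follow-up visits: "To compare the CD4 counts measured at 3 and 6 months among HIV- infected individuals" for CD4, and "To compare the plasma levels of immune activation biomarker (sCD14) measured at 3 and 6 months" for sCD14. P-selectin, activated T cells and exhausted T cells are worded the same way. Section 2.7 adds, for CD4 only, an expectation relative to baseline: "it is expected that the CD4 count will rise by > 30% from baseline value at months 3".

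Section 2.10 shows that every one of these markers has a baseline value: "The baseline investigations will include RFT, LFT, CD4 counts and FBP which are routinely taken before initiation of ART", and the same paragraph adds sCD14, sP-selectin and the T-cell activation and exhaustion markers at baseline. Table 2.1 agrees. Section 2.9.3 states that randomisation is performed separately at each site.

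**The concern.** The plan collects the most obvious predictor of each follow-up value, namely the same marker before treatment, and then fixes a test that does not adjust for it. Two things follow. Confidence intervals are wider than the data require. And if the arms happen to differ at baseline, part of that difference stays in the estimated effect.

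These markers are the trial's mechanistic evidence. Section 1.7 says the trial takes them up because two earlier aspirin studies disagreed on them, so precision here has value. The method is stated in the protocol, so this is a choice that can be assessed and not a detail awaiting a separate analysis plan.

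**Working it through.** **The plan's own figure.** The protocol gives no power or detectable difference for the markers. Its only sample size is for the binary primary outcome: 75% versus 86%, two-sided 0.05, 80% power. The pooled two-proportion formula gives 203 per arm, and 203/0.9 rounds up to 226, against 227 stated. (With the exact 1.15 × 75% = 86.25%, the results are 193 and 215.) The figure is reproduced closely and has no bearing on this point except to supply n. Evaluable patients per arm are 227 × 0.9 = 204.

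**Assumptions.** The baseline-to-follow-up correlation ρ is not given, so 0.3, 0.5, 0.7 and 0.8 are used. Formulas for change scores also assume equal SDs at baseline and follow-up.

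**Which t test?** Section 2.13.3 does not say whether means of follow-up values or of change are compared. Section 1.6.3 suggests follow-up values; the CD4 expectation in section 2.7 is compatible with change. Both are worked.

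**Variance of the arm difference, relative to a t test on follow-up values:**
- t test on follow-up values: 1
- t test on change: 2(1−ρ)
- ANCOVA on own baseline: 1−ρ²

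ANCOVA relative to change is therefore (1−ρ²)/(2(1−ρ)) = (1+ρ)/2. Both ANCOVA ratios are below 1 for every ρ strictly between 0 and 1. The equivalent multiple of patients is the reciprocal of the ratio.

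| ρ | ANCOVA vs follow-up | times patients | ANCOVA vs change | times patients |
|---|---|---|---|---|
| 0.3 | 0.91 (−9%) | 1.1 | 0.65 (−35%) | 1.5 |
| 0.5 | 0.75 (−25%) | 1.3 | 0.75 (−25%) | 1.3 |
| 0.7 | 0.51 (−49%) | 2.0 | 0.85 (−15%) | 1.2 |
| 0.8 | 0.36 (−64%) | 2.8 | 0.90 (−10%) | 1.1 |

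**Detectable difference at 80% power, 204 per arm.** For the t test on follow-up values: (1.96 + 0.84) × √(2/204) = 0.277 SD. Multiply by the square root of the variance ratio for the others.

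| ρ | t on follow-up | t on change | ANCOVA |
|---|---|---|---|
| 0.3 | 0.277 | 0.328 | 0.265 |
| 0.5 | 0.277 | 0.277 | 0.240 |
| 0.7 | 0.277 | 0.215 | 0.198 |
| 0.8 | 0.277 | 0.175 | 0.166 |

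**Chance imbalance.** With 227 per arm the baseline difference has SE √(2/227) = 0.094 SD, so a 95% range of about ±0.18 SD. A fraction ρ carries into a follow-up comparison: 0.03, 0.05, 0.07 or 0.08 SD per 0.1 SD of imbalance at the four values of ρ. A change analysis over-corrects, leaving −(1−ρ) of it: −0.07, −0.05, −0.03 or −0.02 SD.

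Given a baseline imbalance of k standard errors and no treatment effect, the follow-up test statistic has mean ρk and variance 1−ρ². At k = 1.96 the chance of a two-sided p < 0.05 is about 7.9%, 12.9%, 20.5% or 25.7%. At k = 1 it is 5.0%, 4.8%, 3.9% or 2.7%. Averaged over randomisation it is 5%.

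**The case against.** The strongest reply is that randomisation makes the t test valid without adjustment, and that these are secondary outcomes of a phase IIA trial. That stands: a reader might infer that the planned test is biased or inflates type I error, and it does neither. The 12.9% to 25.7% figures at ρ of 0.5 or more are conditional on a large imbalance, and at one SE of imbalance the conditional rate is at or below 5%.

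A second reply is that the size of the gain is unknown. That also stands. No correlation is given, and baseline is before ART while follow-up is on ART; section 1.1 reports higher T-cell activation in untreated patients than in suppressed ones. A high correlation cannot be taken for granted, so the range has to include 0.3. Nor may 2.8 times the patients be quoted alone: it needs both ρ = 0.8 and the follow-up reading of section 2.13.3. If change is analysed, the same ρ gives only 1.1. What does not follow is that there is no gain, since ANCOVA has the smaller variance on either reading.

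A reader might also infer that imbalance passes in full into the effect. Only the fraction ρ does.

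Finally, a reader might extend the point to morbidity, defined under Definitions as the "number of health facility/ hospital visits for medical attention/ care because of illness" and/or the number of admissions, and conclude that a t test of counts would make early leavers look healthier. The protocol does not support this. Section 2.13.3 assigns no test to morbidity, sections 2.9.6.1 and 2.9.6.2 keep withdrawn patients in follow-up where possible, and the arm comparison is materially distorted only if follow-up time differs by arm, which nothing in the document suggests.

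**Conclusion.** The point holds as one of efficiency and conditional imbalance on the continuous secondary outcomes. The unadjusted t test is valid but less precise than an analysis adjusted for baseline, whichever reading of section 2.13.3 is meant.

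That direction needs only a baseline-to-follow-up correlation strictly between 0 and 1. The size rests on the assumed range of 0.3 to 0.8 and, for the change reading, on equal SDs at the two times. The case for change is strongest where the markers are closely correlated over time, and the case for follow-up values where they are not; ANCOVA removes the need to choose.

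The binary primary outcome and the 227 per arm are not touched.

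**What to change.** In section 2.13.3, replace the t test for CD4, sCD14, sP-selectin, CD38/HLA-DR and PD-1 with ANCOVA of the month-3 and month-6 value on arm, the marker's own baseline and site. Work on the log scale where a marker is skewed, and report the adjusted difference, or ratio on the log scale, with its 95% CI. Site belongs in the model because randomisation is separate by site; section 2.11.6 also has month-6 CD4 run in the site laboratories.

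Add one sentence on missing baseline values. Section 2.16 warns that results relying on clinic records may be missing, and baseline CD4 is a routine test.

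The cost is one paragraph, slightly more analysis work and that rule. No new data, visits or patients are needed. The change should be made before the treatment codes are released, so that adjustment is not chosen after results are seen.
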